### Randomisation

Centralised randomisation will be performed with a 1:1 ratio using a computer‐generated sequence. Patients will be randomised either to the interventional or control group after first obtaining their informed consent. Stratified randomisation is performed based on the radiological T and N stages into four groups: T3N‐, T3N+, T4N‐, and T4N+. The attending surgeon will then be informed of the patient's treatment group. When obtaining consent, the attending surgeon will not be aware of the assigned group, as the randomisation will be performed afterwards.

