### Statistical analysis and sample size calculation

Qualitative variables will be described using numbers and percentages. Quantitative variables will be described using the mean and standard deviation, or by median and interquartile range, for normally and distributed data, respectively. The Kolmogorov‐Smirnov test will be used to compare the normality of the variables. All randomised participants will be included in the population‐based intention‐to‐treat analysis. OS is defined as the time from surgery until death from any cause or follow‐up completion. PFS is defined as the time from the randomisation until local or distant recurrence or death.

PFS curves in the two treatment groups will be calculated using the Kaplan‐Meier method and compared using the Mantel Cox test. To determine the adjusted impact on OS and PFS, all clinically significant factors will be included in a Cox multiple regression model, and hazard ratio (HR) will be calculated with a 95% confidence interval. Statistical significance is set at *p* < 0.05. The SPSS version 15 software will be used for this purpose. Global statistical analysis will be performed by the main investigator.

This study is estimated to require 238 patients (119 per group, with a unilateral alpha type one error of 5%, power of 80%, and 5% of dropouts) to test the following hypothesis: Two‐year PFS of 75% and with an expected improvement of 15% in the neoadjuvant group, achieving a PFS of 90%.

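### The stated PFS test does not use the four T/N randomisation strata, and the open covariate rule for the adjusted Cox model admits consequences of NAC and more terms than about 40 events support

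*Protocol article*

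**What the plan says.** The Randomisation section reads: "Stratified randomisation is performed based on the radiological T and N stages into four groups". The groups are T3N-, T3N+, T4N- and T4N+.

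The section Statistical analysis and sample size calculation says that Kaplan-Meier PFS curves will be "compared using the Mantel Cox test". It does not mention the strata. For the adjusted effect on OS and PFS, "all clinically significant factors will be included in a Cox multiple regression model". The factors are not named or counted, are not tied to the strata, and are not confined to variables known before randomisation.

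The same section gives the planning figures: the trial is "estimated to require 238 patients (119 per group"), with a control-arm two-year "PFS of 75% and with an expected improvement of 15% in the neoadjuvant group". It gives no number of events.

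**The concern.** Two things look wrong, and they differ in weight.

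**The test.** Balancing the arms on prognostic groups removes the between-stratum part of the chance difference between arms. An unstratified log-rank variance still counts that part. The test then rejects slightly too rarely under the null and loses a little power, and nothing is gained in return.

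**The adjusted model.** The covariate rule selects on clinical importance, not on timing. The article records several clinically important variables measured after NAC or surgery: post-treatment TNM, tumour volume, RECIST response and pathological response (Tumour response grade), and Clavien-Dindo grade and toxicity (Postoperative morbidity and mortality). The Discussion expects NAC to produce a tumour response and a better R0 rate. Conditioning on such variables removes part of the effect under test and can bias what remains. A rule that takes every important factor also sets no ceiling on model size in a trial with few events. The trial is open label and the main investigator performs the analysis, so an unfixed list leaves the adjusted hazard ratio open to choices made after the data are seen.

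**Working it through.** **1. Planned sample size.** Inputs from the sample-size paragraph: 75% and 90%, 80% power, alpha 5%, 5% dropout.

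- Two-sided, no continuity correction: n = [1.960·√(2·0.825·0.175) + 0.842·√(0.75·0.25 + 0.90·0.10)]² / 0.15² = 99.5, so 100 per arm.
- With continuity correction: (99.5/4)·[1 + √(1 + 4/(99.5·0.15))]² = 112.5, so 113 per arm.
- 113/0.95 = 118.9, so 119 per arm and 238 in total. This matches the article.

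The match needs a two-sided 5%, although the text says "unilateral alpha type one error of 5" per cent. That is a separate matter. Power is therefore shown two-sided below, with one-sided figures where useful.

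**2. Events for two-year PFS.**

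- Planned effect: 113 × (0.25 + 0.10) = 39.6, or 119 × 0.35 = 41.7 with no dropout.
- No effect, both arms 75%: 2 × 113 × 0.25 = 56.5.

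**3. Events per Cox parameter** (10 per parameter is a rule of thumb, not a figure from the article).

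| Parameters | Planned effect (39.6) | No effect (56.5) |
|---|---|---|
| 4 (treatment + 3 stratum terms) | 9.9 | 14.1 |
| 8 | 4.9 | 7.1 |
| 10 | 4.0 | 5.7 |

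Treatment and the strata alone use up the rule-of-thumb allowance under the planned effect.

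**4. Cost of leaving out the strata.** The unstratified test is Z = Σ(O−E)/√ΣV over the pooled data. The stratified test sums O−E and V within each stratum first. Simulations used 113 per arm and 24 months of follow-up. The article gives no stratum sizes or stratum-specific PFS, so these are assumptions.

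First set: prevalences 20/35/15/30%, marginal two-year PFS held at 75% and 90%, two-sided 5%, 4,000 runs each.

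| HR per factor (T and N) | Power, unstratified | Power, stratified | Null rejection, unstratified | Null rejection, stratified |
|---|---|---|---|---|
| 1 | 84.9% | 85.0% | 4.4% | 4.7% |
| 1.5 | 85.8% | 86.0% | 4.8% | 5.1% |
| 2 | 87.1% | 88.0% | 4.1% | 4.7% |
| 2.5 | 85.7% | 87.5% | 3.9% | 4.8% |

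The Monte Carlo standard error is about 0.3 points for a null rejection rate (√(0.05·0.95/4000)), so the small shortfall in the first row is noise. In the last row, one-sided 5% power is 92.0% against 92.8%.

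Second set: equal-sized strata, treatment HR about 0.37.

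- Control PFS 90/80/72/58%: 84.5% against 86.1%.
- Control PFS 93/82/72/50%: 84.7% against 87.5%; at one-sided 5%, 91.6% against 92.9%.

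At the design effect the loss is therefore 0 to about 3 points. A gap of 5 points (58.8% against 63.8%) appears only with the widest strata and HR 0.5. From a 75% control rate, HR 0.5 means 0.75^0.5 = 86.6%, a smaller effect than the planned 90%.

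**5. Adjusting for a consequence of NAC (illustration).** Marginal PFS is 75% and 90%, and there is one adverse pathological factor with an assumed HR of 2 to 4. If NAC reduces its prevalence from 60% to 40% (assumed), adding it to the Cox model moves the treatment HR from about 0.37 to about 0.41–0.45, and power falls by more than 10 points (400 simulated trials). The direction is the point; the size depends on the assumptions.

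**The case against.** The strongest reply is that this is a condensed article. It does not say that the strata are left out, and the full protocol (version 3) or an SAP, neither of them shown, may stratify the test and list the covariates. That stands as far as intent goes, and silence alone would be no finding. But the article does name a test and does state a covariate rule. Both can be judged as written, and a better method is available from data already recorded.

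The unstratified test is also legitimate. It errs on the conservative side, so a positive result would hold. A marginal hazard ratio nearer to 1 than a stratum-conditional one is a different estimand, not an error. The stratum effects used above are assumed, and the CT accuracy quoted in the Discussion (79.1% for T, 73.3% for N) suggests that misclassification may narrow the spread between strata. All of this stands and keeps the first limb small.

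On the model, radiological T and N would probably count as important factors. No post-randomisation covariate is named, and the adjusted analysis supplements the Kaplan-Meier and Mantel-Cox comparison. These points stand too. They limit the reach of the second limb but do not repair a rule that fails to separate baseline variables from consequences of treatment.

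The figure of about 40 events belongs to two-year PFS under the planned effect. Five-year PFS would have more events, and OS events cannot be derived from the article.

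**Conclusion.** The point holds in a limited form and deserves correction before analysis.

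- **Primary comparison:** as written, it does not use the randomisation strata. The cost at the design effect is about 0 to 3 power points, with a slightly conservative test. This rests on assumed stratum sizes and prognostic effects.
- **Adjusted model:** the rule permits adjustment for variables that NAC changes, and permits more terms than about 40 events (about 56 with no effect) can carry. This is the more consequential part, because the adjusted hazard ratio could be biased, overfitted, or both.

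A reader might infer three stronger things that the documents do not support. One is that the primary test is invalid or leaves the trial underpowered: it controls type I error, and its two-sided power is about 85% against the planned 80%. Another is that the plan intends to adjust for pathological or surgical results: the wording allows this but does not plan it. The last is a power loss of about 5 points: that needs a treatment effect smaller than the design effect as well as the widest assumed strata.

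**What to change.** Three changes of wording, made before the final analysis:

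1. State that the PFS comparison is a Mantel-Cox test stratified by the four randomisation groups.
2. Report the treatment hazard ratio and 95% CI from a Cox model stratified by, or adjusted for, the same four groups.
3. Replace the open covariate rule with a short named list of further baseline covariates (one or two for two-year PFS, given the event count), and exclude every variable measured after randomisation. Pathological response, margins and complications can be reported as outcomes instead.

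The strata are already recorded and a stratified log-rank test is a standard option, so sample size, treatment and data collection do not change. The only downside is a little more specification of the analysis.

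### The stated one-sided 5% alpha does not give 238 patients; 238 matches a two-sided 5% test, so the alpha is mis-stated and the success threshold is ambiguous by a factor of two

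*Protocol article*

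**What the plan says.** All the relevant statements are in the protocol article, section Statistical analysis and sample size calculation, except the allocation ratio.

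- Size: "This study is estimated to require 238 patients".
- Group size, error rate, power and dropout: "119 per group, with a unilateral alpha type one error of 5%, power of 80%, and 5% of dropouts".
- Effect: "Two‐year PFS of 75% and with an expected improvement of 15% in the neoadjuvant group, achieving a PFS of 90"%.
- Allocation (section Randomisation): "Centralised randomisation will be performed with a 1:1 ratio".
- Primary comparison: PFS curves are "calculated using the Kaplan‐Meier method and compared using the Mantel Cox test".
- Analysis threshold: "Statistical significance is set at" p < 0.05, with no side named. Hazard ratios are to be reported with a 95% confidence interval.

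No formula is named for the sample size, and nothing in the article reconciles the one-sided alpha of the design with the unlabelled p-value threshold of the analysis.

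**The concern.** Every input needed to recompute the size is printed, and the result is far from 238 at the stated one-sided alpha. Changing the side of the test recovers 238 exactly. That suggests the trial was sized for a two-sided 5% test and then described as one-sided.

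This matters because the side of the test sets the rule for success. A one-sided 5% rule accepts a benefit at a two-sided p of just under 0.10. That is a 5% false-positive rate in favour of neoadjuvant chemotherapy, against 2.5% under a two-sided 5% rule. With one sentence saying one-sided and another giving an unlabelled p < 0.05 beside a 95% interval, a two-sided p between 0.05 and 0.10 could be called either way once the data are known. The trial is open label and the main investigator performs the analysis, so the rule should be fixed beforehand.

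**Working it through.** **Inputs.** From the sample-size sentence: control 2-year PFS p1 = 0.75, experimental p2 = 0.90, Δ = 0.15, power 80% (z = 0.842), dropout 5%. From the section on randomisation: 1:1 allocation. Mean proportion p̄ = 0.825. The z-value for alpha is 1.645 (one-sided 5%) or 1.960 (two-sided 5%).

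**Formulas (per group).**

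- Pooled: n = [z_α √(2p̄(1−p̄)) + z_β √(p1(1−p1) + p2(1−p2))]² / Δ². Here √(2 × 0.825 × 0.175) = 0.5374 and √(0.1875 + 0.09) = 0.5268.
- Continuity-corrected: n_c = (n/4) [1 + √(1 + 4/(nΔ))]².

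**Reproducing the stated figure (two-sided 5%).**

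- n = (1.960 × 0.5374 + 0.842 × 0.5268)² / 0.0225 = 99.5.
- n_c = (99.5/4) [1 + √(1 + 4/(99.5 × 0.15))]² = 112.5, rounded up to 113.
- Dropout: 113/0.95 = 118.95, or 113 × 1.05 = 118.65. Both round up to 119 per group, 238 in total. This matches exactly.

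**The stated alpha (one-sided 5%).**

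- n = (1.645 × 0.5374 + 0.842 × 0.5268)² / 0.0225 = 78.3, rounded up to 79. Dropout: 79 × 1.05 = 82.95, so 83 (166 in total); 79/0.95 = 83.2, so 84 (168 in total).
- n_c = 91.1, rounded up to 92; 92/0.95 = 96.8, so 97 per group, 194 in total.
- Excess of the stated size: 238/194 = 1.23 and 238/166 = 1.43.

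**Other standard formulas.** The log-rank rows use HR = ln 0.90 / ln 0.75 = 0.366 and a mean event proportion of (0.25 + 0.10)/2 = 17.5%, assuming two years of follow-up for everyone. Totals are at 80% power, after division by 0.95.

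| Formula | One-sided 5% | Two-sided 5% |
|---|---|---|
| Pooled | 168 | 212 |
| Continuity-corrected | 194 | **238** |
| Unpooled | 164 | 206 |
| Arcsine | 160 | 206 |
| Log-rank, Schoenfeld | about 150 (25 events) | about 192 (32 events) |
| Log-rank, Freedman | about 174 (29 events) | about 223 (37 events) |

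No one-sided figure exceeds 194.

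**Power with 113 evaluable per group.**

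| Method | One-sided 5% | Two-sided 5% |
|---|---|---|
| Pooled | 91.1% | 84.8% |
| Continuity-corrected | 87.9% | 80.2% |
| Fisher exact | 88.6% | 81.7% |

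The continuity-corrected two-sided value is the stated 80%.

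**The case against.** The two-sided explanation is inferred by fitting. The article names neither a formula nor a continuity correction, and without the correction two-sided 5% gives 210 to 212. The planned test is the log-rank test, and Freedman's log-rank formula at one-sided 5% and **90%** power gives 39.8 events, 39.8/0.175 = 227.4 patients and 227.4/0.95 = 239.4 after dropout, within 1% of 238. On that reading the side is right and the power figure is wrong. One-sided 5% is also a recognised choice in phase II, which is how the Discussion describes this trial. The size is adequate either way, and the side of the primary test may be settled in a full protocol or SAP that is not shown.

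Some of this stands. The origin of 238 cannot be proved from the article, and the trial is not short of patients: on the one-sided reading it simply has more power than stated.

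The rest does not remove the problem. The Freedman route contradicts the stated 80% power, is not exact, and still leaves the sample-size sentence wrong. The two-sided continuity-corrected route changes one printed input and is exact under both dropout conventions. The phase II label could justify a one-sided 5% test, but it does not make that test yield 238, nor does it label the p < 0.05. A further document may settle the rule; it cannot make the printed inputs agree with the printed size.

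**Conclusion.** The concern holds. At the stated 75% versus 90%, 80% power, 5% dropout and one-sided 5% alpha, the two-proportion formulas need 160 to 194 patients and the log-rank formulas about 150 to 174. Against the pooled formula without and with continuity correction (166 to 194), 238 is 43% to 23% too large. If one-sided 5% is really meant, power is about 88% to 91%, not 80%.

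The most economical explanation is a two-sided 5% test with continuity correction, which returns 119 per group and 80.2% power. The consequence lies in the error rate, not in the power: the false-positive rate for benefit is 5% or 2.5% depending on which sentence is followed. This should be corrected before comparative data are seen, because it concerns the success criterion of the primary endpoint.

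The log-rank figures rest on the assumptions of proportional hazards and two years of follow-up for all patients. The two-proportion figures need only the printed inputs.

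**What to change.** In the sample-size sentence, replace the one-sided 5% alpha with a two-sided alpha of 5% and name the method as a continuity-corrected comparison of two proportions. In the analysis paragraph, state that p < 0.05 for the primary log-rank test is two-sided. Keep N = 238. This agrees with the 80% power and the 95% confidence interval already in the text.

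The sponsor should first check this against its original calculation. If a one-sided 5% test was truly intended, the power statement must instead be corrected to what 238 patients give, the formula named, and the p < 0.05 labelled one-sided.

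The cost is one sentence in the protocol, mirrored in the SAP, and no additional patients. The only substantive effect is that a claim of benefit is held to 2.5% in that direction instead of the 5% that a one-sided reading would allow.

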### Participating centres and trial status

As of July 2023, 17 centres in Spain are currently included in the study, with more than 100 patients collected. The trial is expected to finish by June 2025.

This trial is supported by the European Society of Coloproctology (ESCP) and the Spanish Association of Coloproctology (AECP).

### Ethical approval

The study protocol has been approved by the local Research Ethics Committee and the Spanish Agency of Medicines and Medical Devices (AEMPS). Patients will be informed of the possibility of participating in the study and will need to provide written informed consent prior to enrolment. Patients will be able to withdraw their consent at any time without this affecting the medical care they will receive. The study will be performed in accordance with the Declaration of Helsinki. The main investigator at each participating centre will be responsible for patient recruitment and data recording; they will be audited by an independent data monitoring committee. Furthermore, periodic meetings or audits between the principal investigator at each centre and the study coordinator have been scheduled. Annual report of pharmacovigilance will be redacted, according to the Spanish Clinical Research Network.

The authors of this work declare that they have no conflict of interest in association with the present study, and they commit to publish the results even if they are not favourable to the hypothesis.

### Financial report

No financial compensation for participation in the study is foreseen for neither the patient nor the research team.

## DISCUSSION

For LACC, the standard treatment is based on early surgical resection, following oncological criteria, which is complemented with AC. The 5‐year survival rates for stage IIA and IIIC patients, respectively, are estimated to be 66.7% and 12.9%, according to data obtained from the Surveillance, Epidemiology, and End Result (SEER) [23]. Because of these results, the current treatment scheme cannot be considered as curative. The role of NAC in LACC is relatively new, but some recent studies have shown promising results [11, 14, 24, 25]. ELECLA is a phase II multicentre randomised trial which investigates the effectiveness of NAC in patients with LACC. This study evaluates PFS, because it is an accepted endpoint in studies evaluating adjuvant therapy which can correctly assess treatment efficacy and all‐cause mortality in each patient population. Moreover, it is also a suitable surrogate marker for 5‐year OS.

NAC is expected to achieve a tumour response, improve the R0 resection rate, and confirm its chemosensitivity [26, 27, 28]. For T4b tumours, oncological resection is the standard treatment, even considering complete en bloc multivisceral resection, which has been associated with higher postoperative morbidity and a lower percentage of R0 resection, ranging between 40% and 90% [29, 30]. In a recent meta‐analysis published in 2021, NAC was associated with significant margin‐negative resection rates and improved survival in T4 patients [7, 31]. As a result, NAC has been recommended for resectable T4 colonic tumours in the latest NICE (National Institute for Health and Care Excellence) and NCCN guidelines for colorectal cancer [15, 32]. Furthermore, NAC has been suggested to facilitate margin‐negative excision of LACC according to the new American Society of Colorectal Surgeons (ASCRS) guidelines for the management of colon cancer [33]. The recently published mature results from the multicentre FOxTROT phase III study are also in support of NAC; 6 weeks of preoperative chemotherapy in patients with LACC using a combination of cytotoxic drugs, including folinic acid, fluorouracil, and oxaliplatin, with or without panitumumab (a monoclonal antibody), was associated with a higher percentage of free resection margins (94% vs. 89% in the control group, *p* < 0.001) and a 28% lower recurrence rate compared to controls (rate ratio = 0.72; *p* = 0.037) [25].

In locally advanced rectal cancer, the impact of a pathological complete response (PCR) has been assumed to be a predictor of improved outcomes, but this assumption is still debatable for LACC [34]. To address this, Change et al. conducted a prospective observational study of 60 LACC patients who received neoadjuvant treatment and surgery; the PCR rate was higher in T3–T4a versus T4b patients, and PCR significantly improved patient OS [26]. The recent results of the OPTICAL trial, presented at the ASCO 2022 meeting, showed that NAC induced a 7% PCR rate and 20% tumour downstaging rate (pT0‐2N0M0) [35]. Significant tumour regression was also reported in the PRODIGE 22, a French phase II multicentre trial, which randomised 104 LACC patients to curative resection followed by AC or NAC followed by surgery and AC. Patients that underwent neoadjuvant treatment were more likely to achieve tumour remission grades 1–2 (44% vs. 8%, *p* < 0.001) [36]. Moreover, the PCR rate in the FOxTROT trial was 4%, and 62% of patients had some kind of regression. These findings are consistent with the previous published literature [14, 28], but there was no evidence that panitumumab improved the efficacy of NAC in patients with RAS wild‐type tumours [25]. This same trial demonstrated a 5‐year recurrence rate of 30% for those patients with no regression versus 0% in those with PCR, thus highlighting the importance of assessing the correlation between PCR and therapeutic outcomes [25]. These points should be considered when choosing and guiding adjuvant treatment, maybe in combination with the detection of minimal residual disease by circulating tumour DNA [37].

Patient selection and their corresponding therapeutic strategy are determined by CT scan. Several studies suggest that preoperative staging has limited accuracy [38, 39, 40], whereas other support its impact on survival [41, 42]. A significant concern raised from the data collected in these studies is whether preoperative CT staging is accurate enough to avoid overtreatment for low‐risk patients who otherwise would not require NAC or AC. In the preliminary results of the FOxTROT study, only 7% of T2N0 tumours were misclassified [8], although, in the results, 24% of control patients did not meet the criteria for AC [25]. Meanwhile, a Spanish study evaluated the accuracy of CT after NAC, and over staging was observed in 9.1% of cases [43]. In another study published by Huh et al. with more than 500 patients, CT had accuracies of 79.1% and 73.3%, respectively, for T and N staging. Radiological staging was also found to be an independent predictor of long‐term survival and was recommended for selecting patients with CC participating in clinical trials with NAC [42]. Magnetic resonance imaging allows a better soft tissue discrimination and diffusion‐weighted imaging and may become an interesting complementary tool for the selection of patients [44].

Another drawback is the possibility of continued tumour growth despite neoadjuvant treatment. In the FOxTROT trial, 4.3% of patients that received NAC required emergency surgery due to obstruction during preoperative treatment [34]. According to a single‐arm randomised phase II study with 47 patients, none had progression while receiving CapeOX (oxaliplatin plus capecitabine) [45]. Consistent results were observed in another study with 65 LACC patients, with a tumour volume reduction of 62.5%, without any case of progression [14]. In patients that undergo surgery upfront, some factors may encourage the development of micrometastasis and tumour progression, such as the stimulation of growth factors associated with the procedure and immunosuppression during the early postoperative period. In a recent propensity score matching analysis, none of the patients experienced progression, and the incidence of distant recurrence was significantly reduced [46]. NAC could control these potential factors, thereby improving the efficacy of cancer surgery through local downstaging and elimination of circulating tumour cells, potential micrometastases, and lymph node metastases [46, 47].

Although colonic obstruction is an exclusion criterion for NAC in our study, a diverting stoma or a self‐expanding metallic stent, as an alternative to emergency resection, enables improved local and distant tumour staging and the possibility of offering NAC, with its potential benefits [48, 49, 50].

Microsatellite instability is another exclusion criterion in our study. In the FOxTROT trial, the response to NAC was significantly lower in patients with deficient mismatch repair (dMMR) versus proficient mismatch repair (pMMR) tumours (7% vs. 23% moderate or greater histological tumour regression; *p* < 0.001). In addition, reductions in 2‐year recurrence were seen only in pMMR tumours, with no apparent benefit in dMMR tumours [25]. Furthermore, in a pilot study, neoadjuvant immunotherapy in LACC has shown promising results in dMMR tumours, with a 100% response rate [51]. This novel strategy has not yet been implemented in clinical practice or in our study. Larger studies and longer follow‐up are required. In our trial, we have chosen a neoadjuvant fluoropyrimidine‐oxaliplatin regimen without any monoclonal antibodies, as the latter was recently demonstrated to be ineffective in the preoperative setting [25]. Due to its increased toxicity, Irinotecan has not been considered for addition [52]. The rationale for offering three cycles of XELOX, rather than one or two, was to try to achieve maximum response; and rather than more cycles, to minimise the risk of tumour progression, in case of lack of response. The authors of the ELECLA trial have tried to offer a very pragmatic neoadjuvant scheme, looking for a high complementation rate in a real‐world scenario. Consequently, in the control arm, we have decided not to administrate adjuvant chemotherapy in the group of patients with pathological stage II without bad prognostic factors in order to avoid overtreatment, although it might be a bias.

The favourable tumour response to NAC warrants appropriate oncological control, but also results in a lower perioperative morbidity rate, contrary to previous assumptions that it renders patients less fit for surgery. In the FOxTROT trial, NAC did not increase surgical morbidity, but rather, less complications requiring emergency reoperation were observed [25]. A recent Dutch nationwide population‐based study found no significant difference in major complications and OS, which further supports the safety and feasibility of NAC [10]. These promising results, and those including neoadjuvant tolerance, are supported by other similar studies [14, 36, 45, 46, 53, 54]; even in adverse contexts, such as perforated CC [55].

All the initial experiences in the use of NAC for LACC support its feasibility, including a specifically directed study assessing the real‐life experience of implementing FOxTROT in other hospitals. This study also highlights the importance of a multidisciplinary committee [56]. Recent meta‐analyses have indicated that neoadjuvant treatment improves long‐term surgical and oncological outcomes [28, 57, 58]; but the final role of NAC in LACC in the therapeutic guidelines remains unresolved [24, 44, 59, 60, 61, 62]. This is the reason why the authors consider this topic worthy of continued research, as revealed by the ongoing FOxTROT2 and FOxTROT3, OPTICAL or NeoCol trials [63, 64, 65].

